## 3. Objectives and outcomes

We aim to include 150 adults aged 18-55 years from five Mensura EDPB sites. These will be equally randomized in two study arms receiving two doses of:

- Arm 1: 20µg BNT162b2
- Arm 2: 30µg BNT162b2

We aim to include up to 25 previously SARS-CoV-2 infected subjects per arm. The objectives of this study include assessing the immunogenicity (both humoral and cellular), safety and reactogenicity of a reduced vaccine dose.

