#### Discontinuation criteria

All participants retain the right to end their participation in the study at any point in time. Participants who fail to provide the necessary information through the questionnaires, will be discontinued from the study, since any correlation analysis with biological measurements becomes impossible.

The primary objective of the study is to prove non-inferiority of anti-RBD binding antibody titers four weeks after the second dose of the 20µg versus 30µg study arm. If the primary outcome of the study reveals an inferiority of the 20µg dose, participants in the 20µg dose arm will be offered a third, 30µg dose of the study vaccine.

Although no correlate of protective immunity has been validated yet, a relationship between vaccine-induced SARS-CoV-2 antibodies and protection has been proposed (7).

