## Sample size

The primary analysis is a non-inferiority comparison at 28 days after the second dose, for the GMT of antibodies binding to the RBD of SARS-CoV-2, comparing the reference dose (30µg BNT162b2) with the reduced dose (20µg BNT162b2).

Currently available data from published and ongoing COVID-19 vaccination trials indicate that:

- RBD-specific antibody titers (GMT, arbitrary units) 28 days after the second dose of BNT162b2 equals 2125. The standard deviation on the log scale (base 10) is 0.27 (PICOV-VAC trial).

The following assumptions are made in the sample size calculations:

- The non-inferiority margin is -0.15 absolute difference of GMT on log scale (base 10), between a reduced dose and regular dose vaccine schedule.
- The standard deviation of GMT on the log10 scale is 0.27 for BNT162b2, based on the currently available data.
- The true difference of GMT on log10 scale is 0.
- A two-sided 2.5% family-wise error rate (at cohort level).

Based on these assumptions, the comparison between both doses will need a minimum of 50 participants (infection naïve) per group to achieve 90% power. In order to be able to better evaluate reactogenicity however, we aim for a larger sample size.

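### If the ceiling of 25 previously infected per arm is fully used, 75 per arm leaves exactly the stated minimum of 50 infection-naïve, with no room for missing four-week titres

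*Protocol*

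**What the plan says.** Section 3 (Objectives and outcomes) fixes the enrolment: "We aim to include 150 adults aged 18-55 years from five Mensura EDPB sites. These will be equally randomized in two study arms". It adds: "We aim to include up to 25 previously SARS-CoV-2 infected subjects per arm".

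The Sample size section states the requirement for the primary comparison, four weeks after the second dose: "the comparison between both doses will need a minimum of 50 participants", infection-naïve and counted per group, for 90% power. It gives one reason for enrolling more than that: "In order to be able to better evaluate reactogenicity however, we aim for a larger sample size". Missing samples are not mentioned there, and no loss rate appears anywhere in the protocol.

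Losses are nevertheless foreseen. Under Discontinuation criteria, "All participants retain the right to end their participation in the study at any point in time", and participants who do not supply the questionnaire information are taken out of the study. Baseline activities also provides for recording an early end of study.

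Two other sections bear on the point. Trial randomization stratifies by age and gender and disregards infection status. Statistical analyses places every eligible participant in the main analysis, without restricting it to the infection-naïve.

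**The concern.** The minimum of 50 is a requirement on the analysis: that many naïve participants per group must have a four-week titre. The enrolment figures of 75 and 25 concern people entering the trial. At the permitted ceiling the two numbers coincide, so the whole surplus over the minimum consists of previously infected participants, who cannot replace a lost naïve participant in a comparison sized on naïve participants. Any loss among the naïve then takes the evaluable number below the figure on which the power statement rests.

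An analysis plan cannot repair this later, because enrolment size and the infected ceiling are fixed in the protocol.

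**Working it through.** **Inputs.** From section 3: 150 participants, equal allocation, at most 25 infected per arm. From Sample size: minimum 50 naïve per group, 90% power, margin 0.15 and SD 0.27 on the log10 scale, true difference 0, and an error rate given as two-sided 2.5%. Assumed here: one-sided 2.5% for the main figures, and a loss of 2%, 5% or 10%.

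**Step 1: the plan's own figure.** n per group = 2 × [SD × (z₁₋α + z₀.₉₀) / margin]², with SD / margin = 0.27 / 0.15 = 1.8.

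- One-sided 2.5%: 2 × [1.8 × (1.960 + 1.282)]² = 68.1, so 69.
- One-sided 1.25% (the stated error rate read literally): 80.4, so 81.
- One-sided 5%: 55.5, so 56.

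The stated 50 is not reproduced at 90% power under any of these. At one-sided 2.5% it corresponds to roughly 80% power, for which n = 51.

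**Step 2: naïve participants at the ceiling.** 150 / 2 = 75; 75 − 25 = 50 enrolled per arm. Tolerable loss = 1 − 50/50 = 0%.

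**Step 3: below the ceiling.** Tolerable loss = 1 − 50 / (75 − infected).

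| Infected per arm | Naïve per arm | Tolerable loss |
|---|---|---|
| 25 | 50 | 0% |
| 20 | 55 | 9% |
| 15 | 60 | 17% |
| 10 | 65 | 23% |

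**Step 4: cost in power at the ceiling.** Power = Φ(margin / (SD × √(2/n)) − z₁₋α). For n = 50: 0.15 / (0.27 × √0.04) = 2.778; 2.778 − 1.960 = 0.818; Φ = 79.3%.

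| Assumed loss | Expected evaluable naïve per arm | Power, one-sided 2.5% | Points lost |
|---|---|---|---|
| 0% | 50 | 79.3% | – |
| 2% | 49 | 78.5% | 0.8 |
| 5% | 47.5 | 77.3% | 2.1 |
| 10% | 45 | 75.0% | 4.3 |

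At 10% loss the other error rates give a similar drop: 70.4% to 65.3% at one-sided 1.25%, and 87.1% to 83.9% at one-sided 5%.

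**Step 5: ceiling that keeps 50 evaluable within 150.** Ceiling = 75 − 50 / (1 − loss), with the naïve number rounded up.

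- 5% loss: 50 / 0.95 = 52.6, so 53 naïve; 75 − 53 = 22 infected.
- 10% loss: 50 / 0.90 = 55.6, so 56 naïve; 75 − 56 = 19 infected.

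**The case against.** The strongest reply is that 25 is a ceiling and not a target. The trial enrols 150 against a stated need of 100, and nothing in the protocol says the ceiling will be reached. This stands. A reader might infer that the design has no room for loss at all, but the protocol does not support that: the room is nil only when the ceiling is fully used. What remains is that the buffer depends on who happens to enrol, since the surplus is justified only by reactogenicity.

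Retention may also be good. The primary sample falls about seven weeks after the first dose (three weeks between doses, then four). Participants must be employees until the study ends, and an unfinished questionnaire is completed with the nurse at sampling. These features favour the low end of the assumed range, where the cost is 1 to 2 points of power.

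A reader might also compute the chance that none of 100 naïve participants is lost (0.98¹⁰⁰ = 13%, 0.95¹⁰⁰ = 0.6%) and conclude that the primary comparison is all but sure to fail its requirement. That measures the chance of missing a round number. Power does not drop sharply at 49 per arm; one participant fewer in each arm costs under 1 point.

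Nor does the point hold for every minimum. With a minimum of 40, the ceiling would leave 20% slack (1 − 40/50). With 69, 50 naïve falls short before any loss.

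Finally, if the main analysis really takes all eligible participants, up to 75 per arm contribute and 50 has slack. That reading conflicts with sizing on the infection-naïve, and the conflict needs resolving.

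**Conclusion.** The point holds as a conditional and modest one. At its own permitted ceiling, the design enrols exactly the number of naïve participants it says the analysis needs, while foreseeing withdrawals and allowing for none. The cost is about 1, 2 or 4 points of power at 2%, 5% or 10% loss, from a base of 79.3%.

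This rests on the ceiling being fully used, on the primary comparison being among the infection-naïve as the Sample size section implies, on one-sided 2.5%, and on loss rates that are assumed because the protocol gives none. The failure of 50 per arm to give 90% power is a separate and larger matter, but it governs the remedy: an allowance added to 50 would not bring the power to 90%.

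**What to change.** 1. In Sample size, define the minimum as infection-naïve participants with a four-week titre. State an expected loss rate, and give the power at the number expected to be evaluable when the infected ceiling is reached. Correct the base calculation first.
2. If the sponsor keeps 50 evaluable as the target with 150 participants, lower the ceiling in section 3 to 22 per arm at 5% loss or 19 at 10%. State that this protects about 79% power, not 90%. If the ceiling stays at 25, keeping 50 evaluable takes 2 × (53 + 25) = 156 participants at 5% loss or 2 × (56 + 25) = 162 at 10%.
3. If the minimum is corrected, put the new value in the same formula. For 69 evaluable, 5% loss requires 73 naïve per arm (69 / 0.95 = 72.6), which leaves room for only 2 infected. At 10% loss, 77 are needed (69 / 0.90 = 76.7), more than the 75 planned.
4. Because allocation disregards infection status, a per-arm ceiling cannot be guaranteed as written. Apply the cap as a total at recruitment (44 or 38 for the two ceilings in item 2), which holds per arm only on average, or stratify by infection status in Trial randomization.
5. Reconcile Statistical analyses, which includes all eligible participants, with the infection-naïve sizing.

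The cost is a few sentences and, unless the ceiling of 25 is kept, no extra participants. The downside of a lower ceiling is fewer previously infected participants, for whom the protocol states no separate objective.

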## Trial randomization

Subject randomization will be done using statistical software (RStudio). The system will randomly allocate the 150 participants across both study arms (20µg and 30µg) irrespective of their previous SARS-CoV-2 infection status. The recruitment and randomization process will aim to have a balanced representation of age and gender across the study arms. Therefore stratified randomization will be used based on age and gender.

In addition, 20 participants will be randomly selected per study arm (40 in total) from which extra (heparinized) blood will be collected for in-depth cellular immunogenicity analyses (see table 1). This random selection will be done using the same statistical software (RStudio).

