### **Baseline activities**

After the participant has given written informed consent, the research nurse completes the Subject ID log with participant's name, national number and study number. The participant national number is collected and kept on site by the research nurse in the Subject ID log. Each of the participating sites will transfer this local Subject ID log at study closure to the TTP for data linkage, following the procedure detailed in the authorization of the Information Security Committee.

The research nurse creates a new participant in the study eCRF (hosted on LimeSurvey) and enters the date of consent, gender, year of birth, height, weight. They will also register whether the participant has had a past SARS-CoV-2 infection (i.e. positive nasopharyngeal swab, positive serology test).

Once the information is entered by the research nurse in the eCRF, the participant automatically receives an email (subject "Clinical Trial Message" and starting with "Dear Madam, Dear Sir") with a link to the data entry screens for the patient-reported-outcomes (PROMs). In order to have a second identity check, the participant first enters year of birth and their study number.

The research nurse can view the PROMs of his/her subjects and only exceptionally make corrections upon explicit request by the participant. Each such change will be logged and needs a justification. At all times the research nurse can indicate in the system the early end of study (and stop sending emails to the participant to complete the PROMs), e.g. in case of withdrawal of consent, if known to the research nurse. In case of withdrawal of consent, data already collected will be kept in the study data.

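### Allocation ignores previous infection, so balance on it is left to chance and nothing holds the per-arm figures of 25 infected and 50 naïve

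*Protocol*

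**What the plan says.** Section 3 (Objectives and outcomes) plans 150 participants, equally randomized, and adds: "We aim to include up to 25 previously SARS-CoV-2 infected subjects per arm". The Sample size section states that "the comparison between both doses will need a minimum of 50 participants (infection naïve) per group to achieve 90% power". With 75 per arm the two figures fit exactly, since 75 − 25 = 50.

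The Trial randomization section allocates participants "irrespective of their previous SARS-CoV-2 infection status" and names two stratification factors: "Therefore stratified randomization will be used based on age and gender". The 20 participants per arm for the cellular work are a further random selection, with no mention of infection status.

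The information is available before allocation. Under Baseline activities the research nurse creates the eCRF record, and "They will also register whether the participant has had a past SARS-CoV-2 infection". The Statistical analyses section puts every eligible participant, infected or not, in the main analysis, and gives age and gender as examples of the confounders to be considered.

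**The concern.** The protocol treats infection history as material: it sets a per-arm ceiling for infected participants and bases the sample size on naïve participants. It then excludes that variable from the allocation and describes no other means of holding the per-arm figures. The main analysis nevertheless pools infected and naïve participants, and infection status is not among the confounders named.

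If titers or reactions differ by infection history, an uneven split moves the pooled comparison by chance. Under Blinding/unblinding, the primary comparison also decides whether participants are unblinded early, so avoidable error in it has consequences.

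**Working it through.** **Inputs from the protocol.** 150 participants, 75 per arm; up to 25 infected and at least 50 naïve per arm; margin 0.15 log10; SD 0.27 log10; true difference 0; two-sided 2.5% error rate (one-sided 1.25%). **Assumptions.** The total number infected, K, and the infected-naïve gap in log10 titer are not given, so ranges are used.

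**1. The stated minimum.** n per group = 2 × 0.27² × (z₁₋α + z₁₋β)² / 0.15² = 6.48 × (z₁₋α + z₁₋β)². For 90% power this gives 81 at one-sided 1.25%, 69 at 2.5% and 56 at 5%. About 50 (51) results only at one-sided 2.5% with 80% power. The stated 50 is therefore not reproduced for 90% power. That is a separate issue; below, 50 serves only as the protocol's own threshold.

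**2. Chance that an arm exceeds 25 infected.** With a 75:75 split that ignores infection, the infected count X in one arm has P(X = x) = C(K, x) · C(150 − K, 75 − x) / C(150, 75). The ceiling is broken if X > 25 or K − X > 25. With 75 per arm, this is also the chance that an arm has fewer than 50 naïve. At K = 50 only 25:25 complies: P(X = 25) = 0.137, so the chance is 0.86.

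| Total infected K | P(an arm exceeds 25) | P(arms differ by ≥ 6) | P(arms differ by ≥ 10) |
|---|---|---|---|
| 30 | 0.00 | 0.31 | 0.07 |
| 40 | 0.04 | 0.36 | 0.10 |
| 45 | 0.29 | 0.29 | 0.07 |
| 47 | 0.48 | 0.29 | 0.08 |
| 48 | 0.60 | 0.38 | 0.12 |
| 50 | 0.86 | 0.39 | 0.12 |

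The ceiling is at risk only near 50 infected. Differences of 6 or more are common throughout this range.

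**3. Effect on the naïve comparison.** Power = Φ(0.15 / SE − z₁₋α), with SE = 0.27 × √(1/n₁ + 1/n₂). At one-sided 1.25%, a 50/50 naïve split gives 0.704 and a 45/55 split gives 0.699. The loss is about half a percentage point.

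**4. Effect on the pooled comparison.** Shift = (difference in infected counts / 75) × gap.
- Smallest: 6/75 × 0.2 = 0.016 log10, 11% of the margin.
- Middle: 6/75 × 0.3 = 0.024 log10, 16% of the margin.
- Largest: 10/75 × 0.5 = 0.067 log10, 44% of the margin.

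**5. Cellular subset.** If 25 of 75 per arm are infected, 20/3 = 6.7 of the 20 are expected to be. The SD per arm is √(20 × 1/3 × 2/3 × 55/74) = 1.8, so the between-arm difference has SD 1.8 × √2 = 2.6.

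**6. What stratification achieves.** This was simulated with blocks of 4 in four assumed age-by-gender strata, 3,000 runs per setting. At K = 50, adding infection status cuts the mean between-arm difference in infected from 4.7 to 1.3 and its 95th percentile from 12 to 4. The chance that an arm exceeds 25 falls from 0.87 to 0.57 at K = 50, from 0.29 to 0.001 at K = 45, and from 0.04 to 0 at K = 40. Incomplete blocks explain what remains at 50.

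**The case against.** Four counter-arguments deserve weight.

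- **The ceiling.** A reader might infer that the limit of 25 will usually be broken. The documents do not support this: the figure is a maximum worded as an aim, and no infected share is given. The chance passes one half only from 48 infected upward. This stands, and the claim must be conditional.
- **Power.** A reader might infer that falling below 50 naïve undermines the primary comparison. Step 3 shows that it does not. At 50 infected the mean difference of 4.7 leaves the short arm only about 2 below 50.
- **Bias.** Random allocation produces no systematic bias, and an unadjusted confidence interval already allows for chance imbalance. With a gap of 0.3, and taking 0.27 as the SD within each infection group, the pooled SD is √(0.27² + 0.3² × 1/3 × 2/3) = 0.305 and the standard error 0.305 × √(2/75) = 0.050. A shift of 0.024 is then about half a standard error. The harm is avoidable noise.
- **Analysis.** The list of confounders is open-ended, a naïve-only comparison is possible, and the SAP is not shown. The absence of infection status from the protocol's examples is therefore not an error in itself.

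Nor do the documents say that prior infection is the strongest predictor of titer, and the point does not depend on it. None of these arguments supplies a link between the per-arm figures and an allocation that expressly disregards infection.

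**Conclusion.** The point holds in limited form. The protocol sets per-arm figures for infected and naïve participants, and its randomization has no means of keeping them. Whether the ceiling is broken depends on an infected total that the protocol does not state: unlikely at 40 or fewer, likely at 48 or more. Balance on infection is left to chance at any total.

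The consequence is extra chance error in the pooled, reactogenicity and cellular comparisons. For titer it amounts to 11% to 44% of the margin when the arms differ by 6 to 10 infected and the gap is 0.2 to 0.5 log10. That gap is an assumption. The probabilities assume an exact 75:75 split and infection unrelated to the age and gender strata.

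**What to change.** In Trial randomization, replace the words "irrespective of their previous SARS-CoV-2 infection status" with stratification by previous infection (yes/no, as recorded at baseline), together with gender and a coarse age split, in small blocks. Draw the 20-per-arm cellular subset within infection strata. Include infection status in any pooled analysis.

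Then settle what 25 means. If it is a strict limit, also close enrolment of infected participants at 50 in total and complete the blocks in the infected stratum, because stratification alone does not guarantee 25:25. Since 50 is not a multiple of 4, blocks of 4 alone cannot do this. If it is not strict, describe 25 as an approximate target.

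The cost is a change to the randomization program before the first participant, with no extra data or visits. The drawback is more strata in a trial of 150, which is why the age split should be coarse.

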### 3.2. SECONDARY OBJECTIVES AND OUTCOMES

- GMT of RBD-specific binding antibodies at the time of the second dose, six months and one year after the first dose.
- GMT of neutralizing antibody titers against wild type and variant SARS-CoV-2 viruses at four weeks after second dose administration.
- Cellular immunity parameters (i.e. Memory B-cell responses, T-cell responses, etc) at all clinically and biologically relevant time points.
- Safety and reactogenicity of the different vaccine regimens as defined by the severity, duration and amount of adverse events experienced after each vaccine dose.

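### The 40-person cellular subset is drawn without using recorded infection history, so the number of infection-naïve participants in each 20 is left to chance; stratifying the draw would be a cheap, optional improvement

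*Protocol*

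**What the plan says.** - **Size and allocation** (Protocol, section 3): "We aim to include 150 adults aged 18-55 years from five Mensura EDPB sites", and "These will be equally randomized in two study arms receiving two doses of" 20 µg or 30 µg. That is 75 per arm if enrolment is complete.
- **Previously infected participants** (section 3): "We aim to include up to 25 previously SARS-CoV-2 infected subjects per arm". This is a ceiling. The Protocol gives no expected number.
- **Subset rule** (Trial randomization): "In addition, 20 participants will be randomly selected per study arm (40 in total) from which extra (heparinized) blood will be collected", and "This random selection will be done using the same statistical software (RStudio"). Table 1 repeats that the selection is random, 20 per arm. Neither place names a factor for the draw. For the main allocation, the same section stratifies by age and gender and sets infection status aside.
- **Infection history** (Baseline activities): "They will also register whether the participant has had a past SARS-CoV-2 infection". It is therefore available when the subset is formed.
- **Outcome served** (section 3.2): "Cellular immunity parameters (i.e. Memory B-cell responses, T-cell responses, etc) at all clinically and biologically relevant time points". It is a secondary outcome with no stated margin, hypothesis or power.
- **Timing** (Sampling visits and Table 1): heparin blood is taken only from these 40 people, starting on the day of the first dose.

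**The concern.** The Protocol treats infection history as important elsewhere. It caps the previously infected in each arm, and it counts only infection-naïve participants towards the required size of the primary comparison. The cellular subset has no matching safeguard: the cap bounds the mix among the 75 in an arm, but not among the 20 drawn from them.

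Two things are at stake. First, the subsets can differ by chance in the number of previously infected participants, even when both full arms hold exactly the same number. Second, a comparison restricted to naïve participants rests on however many the draw happens to supply. Because the first heparin sample is taken on the day of the first dose, a naïve participant left out of the draw cannot be added later, whatever the analysis.

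**Working it through.** **Plan's own figure.** There is none to reproduce: the Protocol gives no calculation for the 20 per arm.

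**Inputs.** N = 75 per arm and n = 20 drawn per arm are from the Protocol. K, the number previously infected per arm, is known only to be at most 25, so I take K = 25, 20, 15 and 10, equal in both arms. That the draw is simple random is inferred from the absence of any named stratum.

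**Step 1: composition of one subset.** The number infected is hypergeometric (20 from 75, K infected).
- Mean naïve = 20 × (75 − K)/75. For K = 25: 20 × 50/75 = 13.3.
- SD = √[20 × (K/75) × (1 − K/75) × 55/74]. For K = 25: √(20 × 0.2222 × 0.7432) = 1.8.

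**Step 2: two independent subsets.** The difference in infected counts comes from convolving the two distributions. The chance that at least one arm has 12 or fewer naïve is 1 − (1 − p)², where p is the one-arm probability. For K = 25, p = 0.318 and 1 − 0.682² = 0.54.

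| Infected per arm (of 75) | Mean naïve per subset | P(subsets differ by ≥3 infected) | P(differ by ≥4) | P(at least one arm has ≤12 naïve) |
|---|---|---|---|---|
| 25 (ceiling) | 13.3 | 33% | 17% | 54% |
| 20 | 14.7 | 30% | 14% | 19% |
| 15 | 16.0 | 25% | 11% | 3% |
| 10 | 17.3 | 17% | 6% | about 0% |

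**Step 3: precision of a naïve-only comparison.** Half-width = t(0.975, 2n − 2) × SD × √(2/n). The SD of 0.27 log10 is the Protocol's value for RBD-binding IgG, borrowed here because none is given for the cellular assays.
- n = 13: 2.064 × 0.27 × √(2/13) = 0.22
- n = 15: 2.048 × 0.27 × √(2/15) = 0.20
- n = 20: 2.024 × 0.27 × √(2/20) = 0.17

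**Step 4: mixed comparison, unadjusted.** Assume that infected participants respond δ = 0.3 to 0.7 log10 more strongly, which is not in the Protocol. At the ceiling the SD is √(0.27² + (1/3)(2/3)δ²) = 0.305 to 0.426, and the half-width with 20 per arm is 0.20 to 0.27. An imbalance of 4 people shifts the arm difference by (4/20) × δ = 0.06 to 0.14 log10.

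**Step 5: mixed comparison, adjusted for infection history.** With a common within-stratum SD and the same dose effect in both strata, the variance is SD² divided by the sum over strata of n₁n₂/(n₁ + n₂). For a balanced draw the sum is 10. For 5 against 9 infected it is (5 × 9)/14 + (15 × 11)/26 = 3.21 + 6.35 = 9.56, so the half-width grows by √(10/9.56) − 1 = 2.3%. Averaged over all draws, the growth is about 1% for each K in the table. The adjusted half-width stays near 0.17.

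**The case against.** The strongest reply is that most of the apparent harm belongs to an unadjusted analysis. Step 5 shows that once infection history is in the model, a stratified draw narrows the interval by only about 1%. Adjustment is commonly left to the SAP, which is not at hand, and the Protocol already intends to take participant characteristics into account, naming age and gender as examples. This stands for the mixed comparison. It does not help a naïve-only comparison, or one in which the dose effect differs by infection history: there the number of naïve participants drawn sets the precision.

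It can also be said that the Protocol deliberately enrols previously infected people, so a representative subset is a legitimate choice, and that in-depth assays in 40 people for an unpowered secondary outcome are largely descriptive. Both points stand, and they limit the weight of this comment.

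A reader might infer three stronger claims that the documents do not support:
- **The draw typically leaves 12 or 13 naïve per arm.** That holds only near the ceiling of 25 infected. With 15 infected per arm the mean is already 16.
- **The comparison is biased.** Selection is random within each arm, so there is no systematic bias, only chance imbalance.
- **Cellular responses in previously infected people tell little about dose.** Nothing in the Protocol says so. Its own sizing implies only that the two groups should be counted separately.

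**Conclusion.** The point holds as a modest design improvement. The subset draw ignores a factor that is recorded in time to be used, so the naïve count in each 20 is uncontrolled. How much this matters depends on infected enrolment, which the Protocol bounds but does not predict. At the ceiling the naïve-only half-width is about 0.22 log10. With few infected participants the loss is small. A minimum of 15 naïve would secure about 0.20; reaching 0.17 would take an all-naïve subset. These half-widths rest on the borrowed SD of 0.27, and the widening of an unadjusted mixed comparison rests also on an assumed effect of infection. The chance imbalance depends on neither. The affected outcome is secondary, and no statement in the Protocol is contradicted or miscalculated.

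**What to change.** In the section on trial randomization, state that the 20 participants per arm are drawn at random within recorded infection history, with the same quotas in both arms and a set minimum of naïve participants. Fifteen is one workable minimum: at least 75 − 25 = 50 naïve per arm are available even at the ceiling. Table 1's footnote should match. Compare the arms within infection history or adjusted for it, with the cellular value from the day-of-dose-1 heparin sample as covariate; if the SAP already provides for this, only the selection rule needs changing.

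The number of participants, blood volumes and assays stay the same. The costs are practical. The main allocation list carries no infection history, so the subset must be selected by history at enrolment across five sites, before the first heparin sample. There may also be fewer previously infected participants with cellular data.

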## 4. Methods

This is a randomized interventional clinical trial in healthy subjects organized at five sites of Mensura EDPB.

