#### Laboratory data

Blood samples will be collected as indicated in table 1. Serum will be isolated from serum gel blood collection tubes and will be used for:

- SARS-CoV-2 specific binding antibody quantification: using an *in-house* anti-RBD IgG ELISA.
- Neutralizing antibody capacity measurement against the wild type Wuhan strain and at least one variant of concern: using a virus neutralization assay.

Peripheral Blood Mononuclear Cells (PBMC) will be isolated from heparinized blood on the day of blood draw and will be stored in liquid nitrogen for further analyses. These include:

- Memory B-cell responses: using B-cell ELISpot of flow cytometry
- T-cell responses: using intra-cellular cytokine staining

Samples will be collected at the research sites by a research nurse of Mensura EDPB.

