### 6.3. RESOURCES

- Purchase, preparation and transport of material for the study will be foreseen by Sciensano.
- Mensura EDPB will organize the research sites through the occupational physician.
- Lab analyses will be performed at Sciensano, ULB and ITG.
- PBMC preparations will be done by Sciensano, ULB and ITG.
- Epidemiological and laboratory data will be analyzed by the Sciensano researchers.
- A budget of 203 600 € was estimated and approved.

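### The 20 vs 20 cellular subset is drawn without a site or laboratory stratum although three laboratories prepare the cells: unbiased, but open to an avoidable chance loss of precision

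*Protocol*

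**What the plan says.** The Trial randomization section sets out two steps. The main allocation divides 150 participants between the two dose arms, and for balance on demographics the protocol says: "Therefore stratified randomization will be used based on age and gender". The second step is the cellular subset: "20 participants will be randomly selected per study arm (40 in total"). Of its mechanics the protocol says only: "This random selection will be done using the same statistical software (RStudio"). Neither step names site or laboratory. Sampling visits and the footnote to Table 1 repeat the 20 per arm without adding a stratum.

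Participants come from five sites (4. Methods). The cells "will be isolated from heparinized blood on the day of blood draw and will be stored in liquid nitrogen" (Laboratory data). Section 6.3 divides this work: "PBMC preparations will be done by Sciensano, ULB and ITG". Section 7.4 confirms the division, since frozen cells stay in the biobank of whichever laboratory prepared them.

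Memory B-cell and T-cell responses are a secondary outcome (section 3.2). The protocol attaches no margin, power or decision rule to them.

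**The concern.** Isolating and freezing cells are manual steps, and dividing them among three laboratories creates a possible source of variation that the draw does not control. The protocol balances the arms on age and gender but not on this factor, which its own logistics introduce. A comparison of 20 with 20 has little precision to spare.

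The draw is also made once and cannot be rebalanced after blood is taken. Heparinised blood is collected from the same participants at three visits. If each participant stays with one laboratory, which is plausible but not stated, an imbalance in the draw carries through all three time points. At stake is the precision of one secondary outcome, and the possibility that part of the observed arm difference reflects which laboratory handled more of one arm's samples.

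**Working it through.** The protocol gives no derivation for 20 per arm, so there is no stated figure to reproduce.

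**Inputs from the protocol.** 150 participants, 75 per arm; 20 drawn at random per arm; five sites; three preparing laboratories.

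**Assumptions, not in the documents.** Laboratory shares, which site feeds which laboratory, and the size of any laboratory effect (in within-laboratory SDs of the outcome).

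**1. How often is the draw uneven?** Simulation, 8,000 draws per scenario, allocation made without regard to site, three site layouts:

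| Site shares (%) | Sites feeding labs A / B / C | Some laboratory differs by 4 or more |
|---|---|---|
| 20, 20, 20, 20, 20 | 2 / 2 / 1 | 44-45% |
| 34, 33, 11, 11, 11 | 1 / 1 / 3 | 46-48% |
| 60, 10, 10, 10, 10 | 2 / 2 / 1 | 31-32% |

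The range is therefore about 31-48%. A difference of 5 or more occurs in 16-29% of draws. The median largest difference is 3.

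**2. Is the comparison biased?** The same simulation added laboratory effects of 0, 0.5 and 1 SD either side of the middle laboratory. The mean shift in the arm difference was 0 to within simulation error throughout, and the type I error of a two-sided 5% t-test was 4.8-5.2%.

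**3. What does it cost in precision?** Take three equal laboratories, one of which reads lower by δ SD.

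- Variance of the arm difference in that laboratory's share, for two disjoint random samples of 20 from 150: (150/149) × (1/3 × 2/3) × (1/20 + 1/20) = 0.0224, so the SD is 0.150.
- Variance of the 20 vs 20 comparison without any laboratory effect: 2/20 = 0.100, so the SE is 0.32 SD.
- Added variance: δ² × 0.0224.

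| δ | Added variance | Total | Increase | Equivalent loss out of 40 |
|---|---|---|---|---|
| 0 | 0 | 0.1000 | 0% | 0 |
| 0.5 | 0.0056 | 0.1056 | about 6% | 40 − 40/1.056 = 2.1 |
| 1 | 0.0224 | 0.1224 | about 22% | 40 − 40/1.224 = 7.3 |

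**4. Would adjusting for laboratory be enough without balancing the draw?** With counts a and b in a laboratory, n = a + b and d = a − b, the adjusted comparison has information Σ ab/n = Σ (n/4 − d²/4n). This is 10 when balanced. On average d² is 400 × 0.0224 = 8.95 and n is 40/3 = 13.3, so the loss is about 3 × 8.95/(4 × 13.3) = 0.50. The variance ratio is 10/9.50 = 1.05. Adjusting after an unbalanced draw therefore costs about 5% whatever the laboratory effect. That is a clear gain over 22% at 1 SD, but almost none over 6% at 0.5 SD. A balanced draw avoids this cost.

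**The case against.** Simple random selection is a valid design, and stratifying it is a refinement. A reader might infer that laboratory differences will fall unevenly on the two doses and distort the result. The documents do not support that: laboratories are spread evenly in expectation, step 2 shows no systematic shift, and the ordinary standard error already carries this variability. This part of the objection stands in full.

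A reader might also infer from Statistical analyses that only demographics will be adjusted for. That sentence concerns antibody titers and gives age and gender as examples. No model for the cellular outcomes is stated, and a SAP that is not shown may include laboratory, so the absence of a laboratory factor is not a defect of the protocol.

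Nor does any text show a participant's samples moving between laboratories, or laboratories using different methods. Sample handling is referred to a sampling manual and an SOP, neither of which is at hand. The assays on frozen cells might be run in one place, although section 6.3 lists the same three laboratories for analyses without a split by assay. If laboratory is assigned by day or capacity, it cannot be a stratum at the draw.

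What survives is narrower. The protocol itself, not the SAP, fixes the draw, and names no stratum for a factor that its own logistics create. By step 4, later adjustment does not fully replace balancing.

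**Conclusion.** The point holds as a small design improvement, not as an error. The subset comparison is unbiased and its type I error is intact. The cost is chance imbalance, which is likely (4 or more participants in some laboratory in about 31-48% of draws), and a loss of precision whose size cannot be fixed from the documents: 0% with no laboratory effect, about 6% of variance at 0.5 SD and about 22% at 1 SD. The variance figures assume three equal laboratories with one reading differently; the imbalance range assumes that laboratory follows site, which same-day isolation makes plausible but does not establish. The 22% belongs to the largest effect considered and should not be quoted alone.

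Only the cellular secondary outcome is touched. The primary RBD IgG comparison, and the third-dose offer that depends on it, are not.

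**What to change.** In Trial randomization, state that the 20 per arm are drawn within preparing laboratory, or within site if laboratory follows site, with equal numbers per arm in each stratum. With three laboratories, 7, 7 and 6 per arm would do. The count difference is then zero, and additive laboratory effects cancel from the arm difference. Include the same stratum as a factor in the cellular comparisons, here or in the SAP, so that the standard error reflects the balance.

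The cost is a small change to the selection code and two degrees of freedom for three laboratories (four for five sites), with no extra participants or blood. The site-to-laboratory assignment must be settled before the draw. If laboratory cannot be known by then, site is the fallback stratum and laboratory can still be recorded and adjusted for.
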